### 6.2 Level of significance

For all hypothesis testing performed in the Lifestyle study, a p-value of less than 0.05 will be considered to indicate statistical significance.

### 6.3 Randomization, database lock.

The randomization is performed by computer at a central randomization center in the AMC. Randomization will be stratified according to presence or absence of anovulation and center of treatment. Women eligible for the study will be referred to a research nurse. This person is dedicated to counsel eligible patients and will perform randomization and collect follow-up data, but will not perform the experimental intervention. We will collaborate with the research nurses who are involved in the obstetric and urogynaecological consortium. In this consortium large randomized clinical trials are performed. Information on this infrastructure is obtainable from <http://www.studies-obsgyn.nl/>

The study analysis will be performed on the final data that will become available after the database is formally locked.

### 6.4 Study analysis

The primary analysis will be by intention-to-treat. The dataset for this analysis includes all randomized subjects not violating any of the in- or exclusion criteria, who participated in study activities, and for whom post-baseline data is present.

A per-protocol analysis will also be performed, in which drop-out patients will be identified as non-compliant. Information on the primary outcome, i.e. live birth within two years after randomization will be used whenever provided. Patients who drop out of the lifestyle intervention arm will be analyzed in the “usual care” arm in this per protocol analysis.

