### 4. STUDY POPULATION

#### 4.1 Population (base)

All couples suffering from subfertility visiting the clinics participating in the study will undergo a basic fertility work-up including a semen-analysis, an assessment of tubal patency using CAT or HSG, and monitoring of the cycle to assess ovulation. After the work-up has been completed, a fertility diagnosis will be made and a prognosis for treatment independent pregnancy will be calculated (Hunault et al., 2004), followed by a management proposal for the individual couple.

Ovulatory and anovulatory women with a body mass index between 29 kg/m^2 and 40 kg/m^2 will be approached to participate in the present study. After informed consent, they will be randomly allocated to an intervention program to improve lifestyle with a duration of six months, or to "usual care".

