#### 4.2 Inclusion criteria

We aim to include subfertile women with a BMI of 29 kg/m^2 or above. Women have to be between 18 and 39 years old.

Subfertility is defined as failure to conceive within 12 months of unprotected intercourse in couples (where the woman has an ovulatory cycle), as well as couples where the woman suffers from chronic anovulation due to WHO I or II or PCO.

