#### **6.1.1 Main study parameter/endpoint**

The primary endpoint will be a healthy singleton of more than 37 week gestation born after vaginal delivery. The initial analysis, will be done by intention to treat, so we will not make a difference for treatment independent pregnancies and pregnancies that occurred after treatment. Patients who will drop out of the study will be analysed according to their group of randomisation. In a per protocol analysis drop outs will be asked to provide information on the primary outcome, i.e. live birth within two years after randomisation. These drop outs will be analysed as non-compliant.

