### **9.4 Benefits and risks assessment, group relatedness**

The ethical issues pertaining to this project will be discussed by considering the four ethical principles as discussed by Gillon. (37)

**Autonomy:** After the intake consultation and counseling session by the research nurse, the patient is given the choice to participate in the study. This process of informed consent respects her autonomy.

**Beneficence:** The advantages of a weight loss and exercise program in overweight or obese subfertile women (in order to improving chances of conception and eventually taking a baby home) have clearly been shown. Even if the patient does not conceive during the 6 months period, the health benefits of weight loss on the long-term are clearly in the interest of the patient.

**Non-maleficence:** In some reproductive medicine units, overweight or obese subfertile women are counselled and advised to loose weight before treatment is started. By starting this project, fertility treatment in the intervention arm will be delayed for a maximum of 6 months. There is no evidence that this short delay will influence the eventual pregnancy chances. The structured weight loss and exercise program will probably lead to higher spontaneous and therapy induced ongoing pregnancy chances. Patients with overweight or obesity have additional risks during pregnancy. The risks involve hypertension (OR 2.2), preeclampsia (OR 1.8-2.7) pregnancy diabetes (OR 2.2-3.4), cesarean section (OR 1.3-2.4) compared to normal weight women (see appendix table of evidence). These risks are not additionally influenced by fertility treatment. Lifestyle intervention aims to reduce the

involved pregnancy risks and is part of the analysis of this study. The lifestyle intervention *per se* does not involve additional risk to the patients, but reduces the risks of longterm health complications.

Before giving informed consent all eligible women are informed about the risks mentioned before (in writing in the patients' brochure). Women who are considered to be at the highest risk (i.e. those who have pre-existent hypertension or diabetes, or pregnancy induced hypertension, (pre)eclampsia or HELLP syndrome in a previous pregnancy) are excluded from participation. During the study adverse events will be monitored by a SMB.

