#### 5.1.2 Primary efficacy endpoint

The primary endpoint will be a healthy singleton of more than 37 week gestation born after vaginal delivery. The initial analysis will be done by intention-to-treat, so we will not make a difference for treatment-independent pregnancies and pregnancies that occurred after treatment. Patients who drop out of the study will be analyzed according to their group of randomization. In a per-protocol analysis drop-outs from the lifestyle intervention will be analyzed as non-compliant. For the conventional treatment no difference will be made between the per-protocol and the intention-to-treat analysis.

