## 6.6 Efficacy parameters

### Intention-to-treat analysis

The outcomes with respect to pregnancy will be tabulated for both groups. Counts will be presented and percentages will be calculated in relation to the number of started participants. The following outcomes will be described:

- Vaginal delivery of a healthy singleton >37 weeks of gestation (primary outcome, twin or higher order births counted as failure).
- Live births irrespective of term or health status (multiples counted as 1).
- Ongoing and clinical pregnancies (multiples counted as 1)
- Fetal loss: ectopic pregnancy, miscarriage (<16 weeks), still birth (before or after 24 weeks)
- Type of pregnancies: singleton or multiple
- Mode of conception: spontaneous versus fertility treatment (OI, IUI, IVF/ICSI); number of fertility treatment cycles
- Complications related to fertility treatment
- Gestational complications
- Labor and delivery characteristics (including maternal complications)
- Neonatal outcome

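### The SAP's intention-to-treat set is a modified set: it drops randomised women for ineligibility, non-participation or absent post-baseline data, which the protocol does not do

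*Supplement*

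**What the plan says.** SAP 6.4 sets the status and content of the dataset together: "The primary analysis will be by intention-to-treat. The dataset for this analysis includes" only "all randomized subjects not violating any of the in- or exclusion criteria, who participated in study activities, and for whom post-baseline data is present". SAP 6.6, under the intention-to-treat analysis, adds that "percentages will be calculated in relation to the number of started participants". Neither starting nor participating is defined.

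Other parts of the plan describe a wider set. SAP 5.1.2 states: "Patients who drop out of the study will be analyzed according to their group of randomization". The latest protocol says the same in 6.1.1 ("Patients who will drop out of the study will be analysed according to their group of randomisation"), and its section 8.2 calls the primary analysis intention to treat with no filter. SAP 6.1 expects 20% drop-out in the lifestyle arm and says that this is included in the effectiveness analysis. Protocol 6.4 asks women who withdraw for the primary endpoint at 24 months.

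**The concern.** A set that applies conditions after randomisation is a modified intention-to-treat set, whatever its label. Here it decides who enters the primary test, and the SAP plans no analysis of all randomised women, even as a sensitivity analysis.

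Two of the three conditions, participation and presence of post-baseline data, come into being after allocation. Both can depend on arm. The lifestyle arm has six clinic visits and four telephone or mail contacts that a woman can attend or skip and that generate data; usual care has no such programme. A pregnancy or birth is itself post-baseline data, so the third condition can also depend on outcome.

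The eligibility condition could be harmless if violations rested on facts fixed before randomisation and were judged blind to arm. The SAP requires neither. At stake is the protection that randomisation gives the primary comparison.

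**Working it through.** **1. What the sample size assumes about drop-outs.** Inputs from SAP 6.1: 45% v 60%, 20% drop-out in the lifestyle arm, alpha 0.05, power 80%. The protocol summary gives a two-sided test.

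- Diluted lifestyle rate, with drop-outs at the control rate: 0.8 × 0.60 + 0.2 × 0.45 = 0.57.
- Formula (pooled variance, no continuity correction): n = [1.960·√(2p̄(1−p̄)) + 0.842·√(p₁(1−p₁) + p₂(1−p₂))]² / (p₂−p₁)².
- 45% v 57%, p̄ = 0.51: (1.3856 + 0.5907)² / 0.0144 = 271.2, so 272 per group. This is the plan's figure.
- 45% v 60% without dilution: 173 per group.
- Loss to follow-up: 272 × 1.05 = 285.6, against the stated 285 (272/0.95 would give 287).

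The trial was therefore sized for a 12-point difference with lifestyle drop-outs kept in the comparison.

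**2. Whom the SAP 6.4 filter removes.** Reading 6.4 beside SAP 5.1.2 and protocol 6.1.1:

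| Woman | SAP 5.1.2, protocol 6.1.1 and 8.2 | SAP 6.4 |
|---|---|---|
| Took part, gave some post-baseline data, then dropped out | in | in |
| Never took part | in | out |
| No post-baseline data | in | out |
| Found ineligible | in | out |

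The conflict lies in the last three rows.

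**3. Illustration of size.** The documents do not say how many women would be removed or how they would fare, so both inputs are assumptions. Take no true effect (45% in both arms), 285 per arm, and removal from the lifestyle arm only. If a fraction x with success rate q is removed, the remaining rate is (0.45 − x·q)/(1 − x).

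| x | q | Remaining lifestyle rate | Shift (points) | Two-sided type I error |
|---|---|---|---|---|
| 10% | 45% | (0.45 − 0.045)/0.90 = 45.0% | 0 | 5.0% |
| 10% | 30% | (0.45 − 0.030)/0.90 = 46.7% | +1.7 | 6.7% |
| 10% | 20% | (0.45 − 0.020)/0.90 = 47.8% | +2.8 | 9.9% |
| 5% | 30% | (0.45 − 0.015)/0.95 = 45.8% | +0.8 | 5.4% |
| 5% | 20% | (0.45 − 0.010)/0.95 = 46.3% | +1.3 | 6.1% |

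If the removed women did better than average, the sign reverses. With x = 10% and q = 60%, the remaining rate is (0.45 − 0.060)/0.90 = 43.3%, a shift of −1.7. A woman who conceives before starting the programme would be one such case.

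**4. Power with everyone included.** With all 285 per arm analysed at 45% v 57%, power is 81.9%. If 5% per arm are lost and counted as failures, the rates become 0.45 × 0.95 = 42.75% and 0.57 × 0.95 = 54.15%, and power is 77.9%.

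**The case against.** The filter is narrower than its wording may suggest. Women who miss sessions are excluded from the programme, not from the analysis, and drop-outs who took part and gave data stay in their randomised arm. The 20% drop-out assumption is thus largely compatible with SAP 6.4, and the 5% allowance already expects some women to contribute no outcome. Usual care also has study activities: questionnaires for all participants (protocol 5.1, follow-up) and blood samples (SAP 4.2). A control woman can fail to take part too. All of this stands.

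A reader might infer that the rule strips poorly adherent women from the lifestyle arm and so favours the programme. The documents do not support that. They give no number removed and no success rate for those women. The sample size itself gives drop-outs the control rate of 45%; if the removed women shared that rate, the shift would be zero.

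A reader might also infer from the conflicting eligibility passages that women could be moved in or out once results are known. Nothing shows such an intention, and SAP 4.2 states its own criteria once. The fair criticism is that the SAP does not fix how or when violations are judged.

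None of this answers the main point. The dataset is still defined by post-randomisation conditions and still differs from the protocol.

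**Conclusion.** The point holds as a conflict of definition with a possible bias. SAP 6.4 and 6.6 define a modified intention-to-treat set for the primary analysis. Protocol 6.1.1 and 8.2 do not, and SAP 5.1.2 and the sample size have to be reconciled with it. Followed as written, the SAP gives up the comparison of the groups as randomised.

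The size and direction of any bias are unknown. The illustration runs from 0 to +2.8 points for 10% removed at success rates from 45% down to 20%. The upper figure is 2.8/12 = 23% of the difference the trial was sized for. It assumes removal from the lifestyle arm alone and no true effect. Confidence is high on the discrepancy in wording and low on any particular amount of bias.

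**What to change.** 1. In SAP 6.4, define the intention-to-treat set as all randomised women in the arm allocated, regardless of eligibility violation, participation or drop-out.
2. In SAP 6.6, use all randomised women as the denominator.
3. State one rule for missing primary outcomes that fits both the percentages and the Kaplan-Meier analysis, which censors women when they discontinue. A woman with no follow-up who is censored at time zero adds nothing to the log-rank test, so widening the set without such a rule would change little for her. Add a sensitivity analysis to that rule.
4. Keep the filtered set only as a labelled sensitivity analysis, with participation defined and eligibility violations judged blind to arm on pre-randomisation facts.
5. Separately, the sponsor should reconcile the eligibility passages. On BMI, protocol 4.1 has "women with a body mass index between 29 kg/m 2 and 40 kg/m 2 will be approached" and 4.2 has "We aim to include subfertile women with a BMI of 29 kg/m 2 or above". On diabetes and hypertension, the protocol summary and SAP 4.2 name type 1 diabetes and untreated hypertension; protocol 4.3 does not limit its later mention of diabetes to type 1; and 9.4 refers to "those who have pre-existent hypertension or diabetes, or pregnancy induced hypertension" without either qualifier. Protocol 4.2 is silent on both conditions, so it cannot serve as the common reference.

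The cost is a few sentences and no new data collection, since withdrawals are already asked for the endpoint. The estimate may be slightly more diluted. If missing outcomes are counted as failures and 5% per arm are lost, power is about 78%, just under the planned 80%.

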### **8.2 Univariate analysis and multivariate analysis**

The primary analysis will be by intention to treat.

The primary outcome will be analysed by comparing the pregnancy rates in both groups using Kaplan-Meier analysis of time to pregnancy using the Log-rank test. In this analysis, patients will be censored at the time they discontinue or complete the study without getting pregnant. In addition, pregnancy rates and 95% confidence intervals per group will be calculated based on the Kaplan-Meier estimates at various time points. Further analysis of delivery rates over time will be performed using Cox-regression analysis with correction for the stratification variables ovulatory status and treatment centers as well as for confounders. These analyses will also be performed for spontaneous and treatment-induced pregnancies separately. The same analysis will be performed for the secondary outcome ongoing pregnancies. This will include ongoing pregnancies, that have not yet resulted in the birth of a child. Exploratory subgroup analyses of the primary outcome will be performed for spontaneous and treatment-induced pregnancies and for women with a BMI below 35 versus above 35, as well as for anovulatory versus ovulatory women and for women with a waist-hip ratio of above 0.8 versus below or equal to 0.8 and for women who are 36 years or older versus younger than 36 years based on tests of interaction with treatment group.

Additional analysis concerning the influence of HOMA, androgens, adipokines and cytokines on pregnancy chances and recovery of ovulations in anovulatory patients will be assessed using multivariate Cox-regression.

Incidence of complications of treatment and during pregnancy will be compared in both groups using relative risks and 95% confidence intervals.

Quality of life will be analysed using repeated measures analysis of variance

A per protocol analysis will also be performed, in which drop out patients will be identified as non-compliant. Information on the primary outcome, i.e. lifebirth within two years after randomisation will be used whenever provided. Patients who drop out of the lifestyle intervention arm will be analysed in the “usual care” arm in this per protocol analysis.

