## 6. STATISTICAL METHODS AND REPORTING

### 6.1 Sample size

On the basis of the literature the cumulative live birth rate in a follow-up of two years of subfertility treatment will be 45% for the “usual care” group. The lifestyle intervention group is estimated to have a live birth rate of 60%. We expect an improvement of healthy singleton of more than 37 week gestation born after vaginal delivery from 45% to 60% in the intervention group. Drop-out is expected to be 20% in the intervention arm^4 and is included in the analysis of effectiveness. To prove that, we need to include two groups of 272 women to be included (alpha 0.05, power 80%). To account for 5% lost to follow up 285 women will be included per group. In total, 570 women will be included.

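### The per-protocol analysis moves lifestyle drop-outs into usual care: an as-treated regrouping that conflicts with SAP 5.1.2 and can show a false benefit if drop-outs have a worse prognosis

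*Supplement*

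**What the plan says.** SAP 6.4 (Study analysis) sets the main approach: "The primary analysis will be by intention-to-treat". It then adds a per-protocol analysis in which drop-outs are identified as non-compliant, and continues: "Patients who drop out of the lifestyle intervention arm will be analyzed in the" usual-care arm. Section 8.2 of the latest protocol has the same rule: "Patients who drop out of the lifestyle intervention arm will be analysed in the" usual-care arm.

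SAP 5.1.2 (Primary efficacy endpoint) describes the per-protocol analysis differently. It says "In a per-protocol analysis drop-outs from the lifestyle intervention will be analyzed as non-compliant", with no mention of a move to the other arm, and then "For the conventional treatment no difference will be made between the per-protocol and the intention-to-treat analysis".

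SAP 6.6 lists the full set of pregnancy outcomes for the per-protocol analysis, followed by relative risks with 95% confidence intervals. SAP 6.2 applies p<0.05 to all hypothesis testing. The subgroup analyses are labelled exploratory; the per-protocol analysis is not.

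**The concern.** There are two problems.

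First, the SAP defines two per-protocol comparators. Under 6.4 the usual-care group gains the lifestyle drop-outs. Under 5.1.2, read plainly, it stays as randomised. Unless this is settled beforehand, the choice could be made with results in view.

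Second, the 6.4 rule is an as-treated comparison under a per-protocol label. The same women leave one group and join the other, so a prognostic difference between drop-outs and completers counts twice. If drop-outs do worse, the lifestyle rate rises and the comparator rate falls. A programme with no effect could then show a benefit in a table beside the primary result. Nor do the moved women clearly represent usual care: they were assigned to a programme that holds back fertility treatment until it is completed, the target weight is met or BMI falls below 29 (protocol 6.3).

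**Working it through.** **Inputs.** From SAP 6.1: "born after vaginal delivery from 45% to 60% in the intervention group"; "Drop-out is expected to be 20% in the intervention arm"; 272 women per group, raised to 285 for 5% loss to follow-up; alpha 0.05 and power 80%. The protocol summary says the test is two-sided. The success rate among drop-outs, q, is not in the documents and is varied.

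**The plan's own figure.** If drop-outs get the usual-care rate, the lifestyle arm succeeds in 0.8 × 60% + 0.2 × 45% = 57%. With pooled variance and no continuity correction, 45% against 57% needs

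n = [1.960 × √(2 × 0.51 × 0.49) + 0.842 × √(0.45 × 0.55 + 0.57 × 0.43)]² / 0.12² = 272 per group,

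which matches. Then 272 × 1.05 = 285.6, against the stated 285. The plan's arithmetic therefore uses q = 45%.

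**Group sizes.** Drop-outs: 0.2 × 285 = 57. Completers: 228. Usual care is 285 + 57 = 342 under SAP 6.4 and 285 under SAP 5.1.2.

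**Bias with no true effect.** Both randomised arms succeed in 45%.

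- Completers: (0.45 − 0.2q) / 0.8
- Enlarged usual care: (285 × 0.45 + 57q) / 342

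With δ = 0.45 − q, these are 0.45 + δ/4 and 0.45 − δ/6. Moving drop-outs gives a difference of δ/4 + δ/6 = 5δ/12. Excluding them gives δ/4. The ratio is (5/12)/(1/4) = 1.67.

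Example, q = 35%: completers (0.45 − 0.07)/0.8 = 47.5%; enlarged usual care (128.25 + 19.95)/342 = 43.3%; difference +4.2 points.

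Rejection rates are two-sided, from 400,000 simulated trials per row with a pooled z-test on proportions. The normal approximation agrees: the standard error is √(0.45 × 0.55 × (1/228 + 1/342)) = 4.25 points.

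| q | Completers | Usual care + drop-outs | Difference, moved | RR | Rejection, moved | Difference, excluded | Rejection, excluded |
|---|---|---|---|---|---|---|---|
| 55% | 42.5% | 46.7% | −4.2 | 0.91 | 16.4% | −2.5 | 8.7% |
| 45% | 45.0% | 45.0% | 0.0 | 1.00 | 5.0% | 0.0 | 5.0% |
| 40% | 46.3% | 44.2% | +2.1 | 1.05 | 7.8% | +1.25 | 5.9% |
| 35% | 47.5% | 43.3% | +4.2 | 1.10 | 16.5% | +2.5 | 8.7% |
| 30% | 48.8% | 42.5% | +6.3 | 1.15 | 31.2% | +3.75 | 13.5% |
| 25% | 50.0% | 41.7% | +8.3 | 1.20 | 50.0% | +5.0 | 20.2% |

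The intention-to-treat difference is zero in every row, with rejection just under 5%. The table assumes that outcomes are known for all 57 drop-outs, whereas SAP 6.4 uses them whenever provided.

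**The case against.** - **Intention to treat is primary and is untouched.** This stands in full. A reader might infer that the trial's main result is at risk. The documents do not support that: drop-outs stay in their randomised group for the primary analysis, and neither the sample size nor any stated decision depends on the per-protocol analysis. The rejection rates above describe a supplementary comparison.
- **Drop-out prognosis is unknown.** This also stands. A reader might infer that the per-protocol table would probably look positive even if the programme does nothing. That does not follow. The plan's own sample size uses q = 45%, where there is no bias; at 40% the spurious difference is 2.1 points; above 45% it reverses. Rejection reaches one half only when q falls to 25%.
- **SAP 5.1.2 can be read more loosely.** It may mean only that no compliance criterion is applied to women randomised to usual care, which is compatible with SAP 6.4. That reading is possible, but it is not the plain one. The non-compliant label alone creates no conflict; the sentence on conventional treatment does.
- **Drop-outs may receive ordinary care.** Protocol 6.4 sends women who leave the study to local infertility protocols, and protocol 8.2 leaves the course after leaving the programme to the responsible physician. So it cannot be said flatly that they never had usual care, and the length of any delay is not given. This does not make them exchangeable with women randomised to usual care.

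**Conclusion.** The point holds as a should-fix matter. SAP 6.4 and protocol 8.2 prescribe an as-treated regrouping called per-protocol, and on its plain reading SAP 5.1.2 prescribes a different comparator (285 women rather than 342 at 20% drop-out). That conflict needs no assumption about prognosis.

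The possible false benefit is conditional on drop-outs doing worse than the 45% average. It is 5/12 of the gap between that average and the drop-out rate, or 1.67 times the bias from leaving drop-outs out. These sizes rest on 45% success in both randomised arms, 20% drop-out, complete outcome data, and a comparison of proportions rather than of times to event.

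**What to change.** 1. Delete the reassignment sentence from SAP 6.4 and protocol 8.2, so that usual care stays as randomised, in line with SAP 5.1.2.
2. If a per-protocol table that excludes drop-outs is kept, label it exploratory and state that it too is selected on prognosis (+2.5 points at q = 35%, +5.0 at q = 25%, with no true effect).
3. If an effect of completing the programme is wanted, report a complier average causal effect with randomisation as instrument: the intention-to-treat risk difference divided by the completion proportion, with a bootstrap interval, assuming that no usual-care woman takes the programme. At the planning values, (57% − 45%)/0.8 = 15 points, which recovers the planned 60% − 45%. State with it that the method assumes non-completion has no effect on outcome, and that partial exposure and delayed treatment may violate this.

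The cost is a wording change in two documents, best made before database lock, and one optional estimate from data already collected. The complier estimate has a wider interval and rests on an assumption that this trial's design may strain.
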